### Objectives

The objectives of this study are as follows:

1. To evaluate the relative effectiveness of internet-based CBT-I, three different types of CT (light, temperature and physical activity), and the combined application of CBT-I and each of the CT’s, as compared to placebo treatment, on [1] subjective sleep efficiency (primary outcome), [2] subjective daytime functioning, [3] actigraphic sleep estimates, and [4] cost effectiveness.

2. To evaluate whether insomnia subtype moderates the effectiveness of the individual and the combined treatments.

3. To evaluate whether the effect of CBT-I is enhanced by prior CT.

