
In this regression equation, SE = sleep efficiency; ß_0ij_ = intercept; time denotes the post intervention (T1) versus baseline (T0) assessment week; CBT = cognitive behavior therapy assignment; BL = bright light assignment; PA = physical activity assignment; BW = body warming assignment; ISP = insomnia subtype probability; and ß_1_ to ß_31_ denote effect estimates. The effects and terms of interest are shown in bold font. For example, line 2 shows in bold font the overall treatment by time interaction effect **ß**_**8**_ of CBT-I versus waitlist and the moderation of this effect **ß**_**10**_ by one’s insomnia subtype probability. Lines 3 to 5 show the corresponding effect estimates for BL, PA and BW interventions, and lines 6 to 8 the for their interaction with CBT-I. For clarity, the regression equation shows only one of the four expected ISPs. Wald tests will be used to evaluate the significance of the effect estimates. Statistical significance is thresholded at p = 0.05. The simultaneous estimation of all effects of interest in a single regression model compensates for multiple comparisons. Mixed effect model analyses will be implemented in MLwiN (version 2.02, Centre for Multilevel Modelling, University of Bristol, Bristol, UK.) and (R: A language and evironment for statistical computing, R Foundation for Statistical Computing, Vienna, Austria.).

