### Power and sample size

#### Statistical power estimates

The statistical power of mixed effect regression models with seven repeated measures (diaries) both before and after intervention have been calculated according to the equations given by Twisk, page 280 [90], similar to those calculations made in a previous repeated measures RCT that we published [91]. Statistical power calculations on repeated measures require an estimate of the intraclass correlation coefficient (ICC, that is, within-subject). We estimated the ICC for the primary outcome measure of subjective sleep efficiency from the 9-day sleep diaries [67] that we recently assessed through the internet for 27 people suffering from insomnia according to an Insomnia Severity Index ≥10 [92]. In agreement with the robust observation that night-by-night sleep variability is an intrinsic part of the insomnia symptomatology (reviewed in [88]), we found only a moderate ICC of 0.27, supporting the use of repeated assessment of the primary outcome measure to increase statistical power of the design.

Given this moderate ICC of 0.27, seven pre-assessments at T0, and seven post-assessments at T1, the 160 completing participants provide a power 1-beta of 0.80 to allow for the detection, at a significance of alpha = 0.05, of even small to medium main effects of CBT-I (minimal detectable difference d = 0.27 standard deviations), of each of the three CTs (d = 0.31) and of their interaction with CBT-I (d = 0.41). The minimally detectable difference in the time by treatment interaction between any two types of CT is small to medium as well (d = 0.38).

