There is unfortunately no readily available methodology to estimate the minimally detectable moderation effects of continuous variables (insomnia subtype probabilities) on a time by treatment interaction effect on a continuous outcome variable (sleep efficiency). In order to obtain a conservative estimate of minimally detectable moderation effects, we can dichotomize the continuous insomnia subtype probability variable by means of a median split, effectively generating two equal groups. The design then becomes one of three factors, each with two levels: time (T1 versus T0), treatment group (Treated versus Untreated on the specific intervention) and insomnia subtype (high versus low probability) and provides the ratio of available data in the subgroup or interest relative to the other available data, to be used once more in the equations given by Twisk, page 280 [90]. According to this conservative approach of mapping the continuous insomnia subtype probabilities onto a dichotomous variable, the 160 completing participants provide a power 1-beta of 0.80 to allow for the detection, at a significance of alpha = 0.05: of a small to medium moderation effects of insomnia subtype (1) on the time by CBT-I treatment interaction (d = 0.31); (2) on the time by each CT treatment interaction (d = 0.41); and (3) on the difference in the time by treatment interaction between any two types of CT (d = 0.44). The smallest detectable moderation effect of insomnia subtype on the time by combined CBT-I and CT interaction is medium sized (d = 0.55). We follow the convention on effect size given by Cohen [93], who suggested consideration of an effect size d of about 0.2 as “small” and an effect size of about 0.5 as “medium.” With an estimated dropout of 10 %, we will recruit 180 volunteers. The expected 160 completers thus allow for the detection of small to medium effect sizes.

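### The detectable differences for the CBT-I by CT interactions and for all subtype moderation effects compare one subgroup with the remaining participants, so the 80% power claimed for these terms does not hold

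*Protocol article*

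**What the plan says.** Under Statistical power estimates, the protocol article states that "the 160 completing participants provide a power 1-beta of 0.80 to allow for the detection, at a significance of alpha = 0.05" of a CBT-I main effect of d = 0.27, and of effects "of each of the three CTs (d = 0.31) and of their interaction with CBT-I (d = 0.41"). It adds that the "difference in the time by treatment interaction between any two types of CT is small to medium as well (d = 0.38").

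For moderation, the same section splits the subtype probability at its median and says that the resulting design "provides the ratio of available data in the subgroup or interest relative to the other available data", which then enters the same textbook equations. The detectable moderation effects that follow are "on the time by CBT-I treatment interaction (d = 0.31); (2) on the time by each CT treatment interaction (d = 0.41"), then 0.44 for subtype on the difference between two CTs and 0.55 for subtype on the combined CBT-I and CT effect. The section concludes that 160 completers suffice for small to medium effects.

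Two other places fix what is to be compared. The Objectives evaluate the treatments "as compared to placebo treatment, on [1] subjective sleep efficiency (primary outcome"), and the Trial design section makes placebo one of the four CT levels. The regression equation under Treatment effects and moderation estimates has indicators for light, activity and warming, and tests interactions and moderation as product terms with time. The threshold is given there: "Statistical significance is thresholded at p = 0.05".

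**The concern.** An interaction is a difference between two treatment effects, and every cell in it adds variance. It cannot be estimated almost as precisely as a main effect in the same sample. Yet the plan gives 0.31 for the moderation of CBT-I by a half-and-half split, barely above the 0.27 for CBT-I itself. The description of the method points to the cause: a subgroup is weighed against all other available data.

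Much of the trial's purpose rests on these terms. Subtype moderation is Objective 2, and combining CBT-I with CT is part of Objective 1. If the design is taken to have 80% power for small to medium interactions, a non-significant term carries more weight than the data can give it.

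**Working it through.** **Inputs** (Statistical power estimates, unless noted)
- 160 completers. With equal limbs (assumed) this is 20 in each of the eight limbs, 40 per CT level and 80 per CBT-I level.
- ICC 0.27, seven diaries before and seven after, alpha 0.05, power 0.80. Sidedness is not stated; two-sided reproduces the figures.
- Median split of subtype, taken as balanced within limbs.

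**Formula.** The cited textbook page is not at hand, so the formula is inferred from its fit to the stated values:

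d = (1.960 + 0.842) × √(V × Σ 1/n), with V = [1 + 6 × 0.27]/7 = 2.62/7 = 0.3743.

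The single-night variance is set to 1, so d appears to be in single-night SDs.

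**Step 1: reproduce the plan's figures**

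| Effect | Split | Computed | Stated |
|---|---|---|---|
| CBT-I | 80 v 80 | 0.271 | 0.27 |
| CT v CT | 40 v 40 | 0.383 | 0.38 |
| Each CT | 40 v 120 | 0.313 | 0.31 |
| CBT-I × CT | 20 v 140 | 0.410 | 0.41 |
| Subtype × CBT-I | 40 v 120 | 0.313 | 0.31 |
| Subtype × CT | 20 v 140 | 0.410 | 0.41 |
| Subtype × (CT v CT) | 20 v 60 | 0.443 | 0.44 |
| Subtype × CBT-I × CT | 10 v 150 | 0.560 | 0.55 |

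The last is off by 0.01. In the seventh row the remainder is the other 60 people in the two CT arms concerned, not the whole trial.

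**Step 2: use the cells of the product terms.** The formula is the same, with Σ 1/n over all cells. Power at the stated d is Φ(d/SE − 1.96), with SE = √(V × Σ 1/n). Two variances are used:
- the plan's own, V = 0.3743;
- a change-score variance, V = 2(1 − 0.27)/7 = 0.2086, which assumes that the ICC of 0.27 also holds from T0 to T1.

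Example, CBT-I × CT with four cells of 20: SE = √(0.3743 × 4/20) = 0.274. The detectable d is 2.8016 × 0.274 = 0.77, and power at 0.41 is Φ(1.50 − 1.96) = 32%.

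| Effect | Cells | Stated d | Detectable d, plan's V (power at stated d) | Detectable d, change score (power at stated d) |
|---|---|---|---|---|
| CBT-I × CT | 4 × 20 | 0.41 | 0.77 (32%) | 0.57 (52%) |
| Subtype × CBT-I | 4 × 40 | 0.31 | 0.54 (36%) | 0.40 (57%) |
| Subtype × CT | 4 × 20 | 0.41 | 0.77 (32%) | 0.57 (52%) |
| Subtype × (CT v CT) | 4 × 20 | 0.44 | 0.77 (36%) | 0.57 (58%) |
| Subtype × CBT-I × CT | 8 × 10 | 0.55 | 1.53 (17%) | 1.14 (27%) |

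A baseline-adjusted variance is more favourable still. With r = 0.27/0.3743 = 0.721, V = 0.3743 × (1 − r²) = 0.1795, and power is 58%, 64%, 58%, 64% and 31% in the same order.

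**Step 3: a check that does not depend on V.** CBT-I has Σ 1/n = 2/80 = 0.025. Its moderation by a half split has 4/40 = 0.100. The standard error doubles, so the detectable d must be 2 × 0.27 = 0.54 beside the plan's own 0.27, not 0.31.

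**Step 4: CT versus placebo.** This is 40 v 40, as is CT versus CT. Under any one variance the two must share one figure, but the text has 0.31 and 0.38. Power at 0.31 for 40 v 40 is 62% with the plan's V, 86% with the change score and 91% baseline-adjusted.

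**The case against.** - **The comparator could be everyone not given that CT.** The moderation paragraph does describe groups as treated or untreated on the specific intervention, and 0.31 is right for a 40 v 120 comparison. This stands for the CT main effect as a possible reading, although it conflicts with the placebo comparison in the Objectives. It does not rescue the interactions: with cells of 20, 20, 60 and 60, CBT-I × CT and subtype × CT still need 0.63 (0.47 with the change score), and power at 0.41 is 45% to 76% across the three variances.
- **The plan's V ignores the baseline diaries.** It is the variance of one seven-night mean, whereas the primary outcome is a change from week 0 to week 5. This stands, and it is why a range is given. It also means that a reader might infer that the CT main effects are underpowered, which the document does not support: the answer turns on the variance chosen.
- **The replacement values are not unique.** This stands. The coding of the indicators is not stated. With 0/1 coding the light-by-time term would be a 20 v 20 comparison within the waitlist at a subtype probability of zero. The figures above show the size of the shortfall and are not a table to copy in.
- **A median split discards information, so calling it conservative is fair.** True of the split. If a continuous, normally distributed moderator is assumed, detectable d falls by about 20%. On the plan's V that gives 0.43 for subtype × CBT-I, 0.61 for subtype × CT and 1.22 for the three-way term, still well above the stated values. Only subtype × CBT-I comes near its stated value (0.30–0.32), and only if that gain is added to a favourable variance. The optimism comes from the subgroup-versus-rest ratio.
- **The effect-size benchmarks.** One might also infer that reading d against the conventional small and medium labels is itself a serious error. That is a lesser matter of presentation, met by stating the SD unit.

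**Conclusion.** The concern holds for the five interaction and moderation figures. As the plan calculates them, they do not describe the terms that its model tests. On the plan's own variance the detectable effects are understated by a factor of about 1.7 (0.77/0.44) to 2.8 (1.53/0.55). The claimed 80% power at the stated d is 17–36% on that variance, 27–58% with a change score and 31–64% baseline-adjusted.

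This rests on equal limbs, a balanced half split, a two-sided test, an inferred formula that matches all eight stated values to within 0.01, and, for the two more favourable variances, an ICC that carries over from T0 to T1.

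For each CT against placebo, only an inconsistency is established: 0.31 and 0.38 are given for the same 40 v 40 contrast. The CBT-I figure (0.27) and the CT v CT figure (0.38) follow from the plan's formula as proper two-group contrasts.

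**What to change.** In Statistical power estimates:
1. Define each contrast behind a stated d, with its comparator and the coding of the treatment indicators and subtype probability. Name the variance used and whether it relies on the ICC holding from T0 to T1.
2. Recompute and restate the detectable d for the interaction and moderation terms on that basis, giving the range: about 0.77, 0.54, 0.77, 0.77 and 1.53 on the present variance, and 0.57, 0.40, 0.57, 0.57 and 1.14 for a change score.
3. Give CT versus placebo the same figure as CT versus CT under whichever variance is chosen.
4. State the SD unit of d.
5. Remove the statement that 160 completers give 80% power for small to medium interaction and moderation effects. Describe only the median split as conservative, not the moderation figures obtained from the subgroup-versus-rest ratio.
6. State that null interaction and moderation results will be interpreted through their confidence intervals.

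The cost is a rewritten power section with less favourable figures. The sample size stays at 160, and treatments, assessments and the primary outcome do not change.

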## Discussion

The ultimate goal of this study is to develop a personalized treatment protocol for insomnia disorder. Primary caregivers could use this protocol to decide on the primary choice treatment for each individual patient. Assessment of insomnia subtype probabilities using the Sleep Subtype Survey results in four ISPs, which can be used to determine the expected treatment outcome of each of four treatments, their combinations and their simultaneous versus sequential application for the individual patient.

Since all treatments used in this study are noninvasive, easily applicable at home and require only the use of a computer and Internet (CBT-I) and/or a readily available therapy light (BL), the implementation of treatments is straightforward, low-cost and scalable.

The current study addresses multiple opportunities to optimize and personalize treatment of insomnia disorder. First, no prior study has evaluated the relative effectiveness of CBT-I, the three different forms of CT, and their simultaneous or sequential combinations. Second, the moderation of outcome by insomnia subtype probability follows the principles of personalized and stratified medicine. Treatment effects with subtype-specificity may come to light that would have remained hidden in the unrecognized heterogeneity of the samples.

## Trial status

Recruitment started in October 2013 and is ongoing. In January 2014, the first participants enrolled. Currently, 60 participants have completed the protocol.

## Abbreviations

APS: arousal predisposition scale
ARSQ: Amsterdam resting state questionnaire
ASRS: ADHD self-report scale
BL: bright light treatment
BW: body warming treatment
CBT: cognitive behavioral therapy
CBT-I: cognitive behavioral therapy for insomnia
CSD: consensus sleep diary
CT: chronobiological treatment
DI: deactivated ionizer
DBAS: dysfunctional beliefs and attitudes towards sleep
DSISD: Duke’s Structured Interview for Sleep Disorders
DSM-V: diagnostic and statistical manual of mental disorders, 5th edition
EMA: early morning awakening
GSES: Glasgow sleep efficiency scale
HADS: hospital anxiety and depression scale
HAS: hyperarousal scale
HDNI: high density negative ionization
ICC: intraclass correlation coefficient
ICSD-2: international classification of sleep disorders, 2nd edition
ID: insomnia disorder
ISI: insomnia severity index
ISP: insomnia subtype probability
OR: odds ratio
PA: physical activity treatment
PANAS: positive affect, negative affect scale
PSAS: pre-sleep arousal scale
SCN: suprachiasmatic nucleus
SE: sleep efficiency
SF-36: short form 36
SLOC: sleep locus of control
SOL: sleep onset latency
SSES: sleep self-efficacy scale
TEPS: temporal experience of pleasure scale
TEPS: temporal experience of pleasure scale
TiC-P: Trimbos/iMTA questionnaire for costs associated with psychiatric illness
WASO: wake after sleep onset
